## Abstract

**Background/Objectives**: Members of the LGBTQ+ community often have poorer health outcomes and less access to health services than cisgender and heterosexual populations, and many healthcare professionals remain insufficiently aware of the barriers faced by these patients. Community nurses, given their skills and competencies, can help patients overcome barriers and achieve greater inclusion. The aim of this project is to identify the barriers and facilitators detected by the primary care nursing team of the Málaga-Valle del Guadalhorce Health District (MVGHD) when providing holistic care to LGBTQ+ individuals. **Methods**: A sequential explanatory mixed-methods design (DEXPLIS) will be employed to robustly combine a quantitative baseline of professional attitudes with an in-depth qualitative exploration of institutional discourses. Phase I consists of a pilot cross-sectional study with cluster allocation of questionnaire versions in which primary healthcare nursing staff in the MVGHD will complete the validated Sexuality Attitudes and Beliefs Survey (SABS) with one group completing a version framed around LGBTQ+ patients and the other around the general population. Phase II consists of a qualitative descriptive study based on discourse analysis (DA) using in-depth semi-structured interviews, analyzed with ATLAS.ti 23. **Conclusions**: This study protocol is expected to provide an empirical framework to identify potential institutional barriers and attitudinal biases in nursing care, highlighting the potential need for targeted training programmes in sexual and reproductive health. The resulting protocol aims to contribute to health equity by offering practical resources to optimize ongoing clinical education in primary care settings.

## 1. Introduction

Under Spanish legislation, Organic Law 10/2022 [1] regulates labour rights and obligations regarding sexual freedom, raising awareness and the defence of physical and moral integrity in the workplace. Among the competencies required in primary healthcare is that of responding to different patterns of human sexuality [2], promoting its assessment and the development of instruments for appropriate intervention and health education for different stages of life.

According to the World Health Organization [3], gender is a social factor that, together with sexual orientation, is associated with healthcare inequalities. Indeed, the WHO considers it essential to incorporate the gender perspective into healthcare in order to improve inclusion and empowerment policies for the entire population. The WHO defines health inequalities as conditions influenced by social, political and economic context and resulting from an unequal distribution of resources among people from different countries and cultures, affecting people’s standard of living, life expectancy, risk of illness and access to treatment and care.

The term LGBTQ+ refers to a group of people whose sexual orientation differs from that of heteronormativity, in terms of sex and/or gender [4], i.e., the multiple dimensions of lesbian, gay, bisexual, transgender and queer (or questioning) populations. Lesbian and gay people are women and men, respectively, who have sexual and emotional relationships with their peers, while bisexuals are those who may be physically and sexually attracted to another person regardless of their gender [5]. A transgender individual is someone who experiences an incongruence between the sex assigned at birth and their gender identity. The term non-binary encompasses the entire population that does not conform to the classical binary standards of gender (woman/man).

The term heteronormativity (or cisheteronormativity) refers to two assumptions: on the one hand, that everyone has a sexual orientation towards their opposite sex/gender; and on the other, that everyone conforms to and identifies with the sex they were assigned at birth [6,7]. In accordance with these premises, any sexual orientation or gender identity that deviates from these norms is often socially positioned as inferior; it is perceived as a threat and must be internalized.

Compared to the cisheteronormative population, the LGBTQ+ community has poorer health outcomes, with higher rates of anxiety, depressive disorders, suicide attempts, substance abuse, eating disorders, chronic diseases such as colon and gynecological cancers, and obesity and sexually transmitted diseases, due to late diagnosis, among other biopsychosocial impacts [8]. Another relevant factor is that of the medical and other complications that may arise from sex-change interventions.

At different stages of their lives, members of the queer community have specific vital needs which, in many cases, are not met [9]. Furthermore, they may experience insecurity and discomfort when receiving healthcare, which provokes a reluctance to engage with the health service [8]. The main reason for this unease is that in many instances the system, too, assumes gender heteronormativity and routinely imposes it.

To a large extent, the sexual and reproductive healthcare inequalities experienced by the LGBTQ+ community arise from discrimination based on gender identity and sexual orientation [10,11,12]. This discrimination is especially apparent in the actions of healthcare personnel, among whom nurses are the largest group and the most influential in this respect. Therefore, it is essential to identify and overcome such barriers to healthcare access and to propose inclusive alternatives.

The Spanish healthcare system is currently facing significant economic and social challenges that directly impact the health of the population. In primary care, appropriate nursing attention underpins patients’ relations with the system and fosters lasting confidence [13]. At this level, preventive medicine is delivered via health education, which should be provided within all social contexts and be free of discrimination [14,15,16].

Primary care nursing is usually the first point of reference for healthcare services [13], including those concerning sexual and reproductive health. In this respect, comprehensive but focused training for nursing staff is needed to ensure that sexual health issues are considered and treated in accordance with the specific needs and idiosyncrasies of the patient. However, studies have highlighted a lack of essential knowledge and professional experience among nurses regarding the sexual and reproductive needs of the LGBTQ+ community [17,18,19,20], partly due to inadequate training in this area.

The provision of holistic, integrated and personalized healthcare for LGBTQ+ patients is hampered by a lack of human and material resources, clinical practice guides and continuing education. In many cases, therefore, the health system environment fails to support the reproductive and sexual care of this population and does not structurally address the barriers they face [21]. Furthermore, many primary care nurses lack confidence and/or experience difficulty in addressing this population in order to provide them with essential health services, probably due to the non-development of appropriate skills and to limited knowledge about the sexual issues involved.

The cultural and religious influence on the sexual and reproductive care provided to LGBTQ+ patients both arises from and feeds back into the culture of addressing sex as a taboo subject in society, an attitude from which nurses are not exempt [22]. Specifically, members of the queer community describe having been subjected to discriminatory, prejudiced or stereotyped behaviours due to their sexual orientation or gender nonconformity. Another area about which many nurses are inadequately informed is that of fertility or reproductive options for this community, a matter of great importance to the individuals concerned [23].

In clinical manuals, homosexuality and transsexuality have historically been conceptualized as pathologies, a label that has led to unequal treatment and reinforced discrimination and stigmatization. The inclusion of these terms in medical classifications has not only legitimized their consideration as disorders but has also influenced social perceptions and the creation of structural barriers to these individuals’ recognition and rights.

In the 1973 edition of the Diagnostic and Statistical Manual of Mental Disorders (DSM) [24], homosexuality was no longer considered a disease, but it remained present under the category of ego-dystonic homosexuality until 1986, perpetuating the idea that this was a condition requiring clinical intervention. It was not until 1992 that the WHO definitively removed homosexuality from the International Classification of Diseases (ICD) [25], a milestone in depathologisation.

By contrast, transsexuality has undergone multiple changes in terminological and diagnostic criteria, which have sustained its pathologisation to this day. In the 1980 DSM-III [26], transsexuality was defined as a disorder, underlining its association with mental illness. Although the classifications have evolved, the concept remains present in the manuals, and in ICD-11 [27] it is reformulated under the term “Gender Incongruence.” While this represents progress, it maintains the idea that such identities require a medical diagnosis.

The persistence of these classifications has had direct consequences on the ways in which LGBTQ+ patients are perceived and treated, which has affected their access to rights, health services and legal recognition [28]. In response, calls have been made to question the effects of this pathologisation and to promote approaches that respect diversity, avoiding the imposition of medical categories that perpetuate inequalities.

The nurse Madeleine Leininger [19,29] has discussed the fundamental impact of culture on healthcare, observing that the beliefs of the nursing team undoubtedly influence the provision or otherwise of holistic and culturally competent care. From an anthropological perspective, these dynamics can be further understood through Mark Nichter’s framework of “Idioms of Distress,” which highlights how culturally standardized communication formats and structural stressors shape how vulnerable groups express suffering and engage with health services. In this context, healthcare barriers and heteronormative practices do not act in isolation; rather, they form a syndemic framework where structural discrimination, clinical training deficits, and social stigma interact to multiply health inequities in the LGBTQ+ population. Furthermore, an intersectional approach is required to acknowledge that these barriers are significantly modulated by age. Sexual communication, perceived barriers, and reproductive healthcare needs differ substantially across the lifespan. Older LGBTQ+ individuals often experience a double burden of ageist stereotypes and cisheteronormativity, which deeply conditions both the attitudes of health professionals and the patients’ actual access to care [30]. Therefore, raising awareness of the queer experience through an intersectional, syndemic lens would facilitate a better approach to sexual and reproductive care.

In the absence of such advances, the present reality often consists of minimal, unsafe healthcare and services, a lack of confidence among medical professionals and rising levels of harmful sexual behaviour and sexually transmitted diseases in the LGBTQ+ population [31]. The root of such problems lies in the heteronormative, patriarchal and hegemonic perspective too often adopted by nurses in their approach to and treatment of this community, thereby generating a climate of distrust and unease [17,18,20]. In general, models of heterosexual activity are still assumed and applied according to “traditional” criteria without addressing the specific needs and peculiarities of other populations, for example regarding contraception methods or hormone replacement therapies, which may be associated with unwanted events and malpractice.

From the evidence currently available, we conclude that there remains a significant gap in scientific knowledge regarding the precise mechanisms through which primary care nursing professionals deliver sexual and reproductive care to the LGBTQ+ population. While general healthcare discrimination is widely reported, there is a distinct lack of protocols designed to capture how local professional discourses, heteronormative communication frameworks (“idioms of distress”), and intersectional age dynamics operate synchronously as invisible barriers within community nursing consultations. This study addresses this specific knowledge gap by mapping both explicit self-reported attitudinal barriers and underlying symbolic resistances within professional practices.

## 2. Rationale

Calls are widespread within the LGBTQ+ population, of all ages, for nurses to provide up-to-date evidence-based sexual education, the absence of which is the main barrier to their accessing appropriate healthcare services [32,33]. This demand creates an opportunity for nursing personnel to raise awareness and actively engage with this target population, fostering their participation in the healthcare system by addressing their sexual and reproductive needs.

In view of these considerations, the present research project is aimed at exploring and addressing the major challenges facing nurses in the administration of basic care and meeting specific needs related to sexuality and human reproduction in the queer community. This process is of essential practical value in terms of clinical care since the identification of specific barriers and needs would facilitate training in this field and enhance professional practice, directly benefiting the health of these patients [34].

Since 2011, the Nursing Degree course offered at the Faculty of Health Sciences of the University of Malaga has included Gender and Sexual Health as a compulsory subject within the Basic Training syllabus (6 ECTS credits) with the following main objective: “*To acquire basic knowledge regarding gender and human sexuality, and to reflect on one’s own attitudes and those of others, to help develop a critical, open and tolerant outlook in this respect*” [35]. Another subject that has been taught since the same year is that of Transcultural Care. This also forms part of the Basic Training syllabus and is eligible for 6 ECTS credits. The main goals of this teaching are to “*equip students with the knowledge, skills, abilities and attitudes necessary to achieve the specific cognitive, procedural and attitudinal competencies required to deliver comprehensive, high-quality care to culturally diverse people, families and communities, from a transversal and multidisciplinary standpoint*” [36].

Despite the potential benefit of this university teaching, it remains essential to address the root cause of the present situation in the healthcare system. The scientific and social relevance of the proposed study lies in the sample of participants targeted, namely primary care nursing staff working in the MVGHD. These professionals were selected for study because they represent a basic pillar of healthcare and because their views directly reflect the impact of prior training [36,37]. Furthermore, in the absence of sensitivity training and comprehensive information on the question, graduates entering the nursing profession will continue to reproduce the shortcomings currently experienced by the LGBTQ+ community. In our opinion, it is of the utmost importance to identify the present gaps and needs in the area of sexual and reproductive education, to demonstrate the potential health benefits of remedial action, and to offer practical resources to those responsible for ongoing clinical training.

## 3. Objectives

The overall goal of this research project is to analyze whether differences exist in primary care nursing approaches to human sexuality counselling depending on whether the care is explicitly directed toward LGBTQ+ individuals or the general population.

### 3.1. Specific Objectives and Outcome Hierarchy

To ensure methodological clarity and consistency, the specific objectives of this sequential explanatory mixed-methods protocol are organized into primary and secondary outcomes across both phases:

#### 3.1.1. Phase I: Quantitative Component (Pilot Cross-Sectional Survey)

Primary Outcome: To evaluate and compare self-reported attitudinal barriers and perceived comfort scores among primary healthcare nursing professionals when providing human sexuality counselling, as measured by the total and dimensional scores of the Sexuality Attitudes and Beliefs Survey (SABS).Secondary Outcome: To estimate the statistical relationship between these sexuality-related attitudes/beliefs and key sociodemographic and professional variables (specifically age, sex, years of experience in primary care, and previous training in sexual diversity).

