#### 4.2.3. Study Variables

Study variables include those related to the biopsychosocial characteristics of nursing professionals (age, sex, educational level, sexual orientation, primary care centre, employment type and years of experience in primary care) collected via an ad hoc questionnaire and the 12 items of the SABS scale (Table 1) [34].

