#### 4.2.4. Procedure, Sample Size and Data Analysis

The validated Sexuality Attitudes and Beliefs Survey (SABS) [34] will be used as the measurement instrument. The sample will be divided into two groups:Group A: Nursing professionals who complete the SABS scale with a brief introduction making specific reference to the sexual and reproductive care of LGBTQ+ individuals.Group B: Nursing professionals who complete the SABS scale with a brief introduction referring to the sexual and reproductive care of the general population, without specifying sexual orientation or gender identity.

Data collection procedure:Initial contact will be made with the heads of the health centres to inform them of the study objectives and obtain institutional consent. Following acceptance, cluster allocation will be performed to generate two groups (Group A and Group B). To ensure maximum methodological rigour, the cluster allocation sequence will be generated by an independent statistical researcher who is completely external to data collection and recruitment. The generation will be performed using a computerized random number generator. Allocation concealment will be maintained at the institutional level: health centres will be assigned to either Group A or Group B simultaneously, and participating nurses will be blinded to the existence of an alternative version of the survey, mitigating potential performance or social desirability biases.The SABS scale will be used to evaluate attitudes and beliefs around human sexuality in nursing, with the aim of detecting obstacles in sexual counselling and recommendations.

The complete survey comprised: (1) an ad hoc section collecting sociodemographic data (age, primary care centre, nationality, sex, sexual orientation, educational level, employment type, and years of experience in primary care), and (2) 12 SABS items rated on a five-point Likert scale (1 = Strongly disagree to 5 = Strongly agree). The survey will be distributed electronically via the LimeSurvey platform, with biweekly reminders to maximize response rates.

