## Figures and Tables

**Table 1 healthcare-14-02416-t001:** Study variables.

Variable	Classification	Values	Source
Randomisation group	Dichotomous qualitative	Group A Group B	Ad hoc questionnaire
Sex	Polytomous qualitative	Female Male Prefer not to say	Ad hoc questionnaire
Age	Discrete quantitative	20–29 30–39 40–49 50–59 ≥60 years	Ad hoc questionnaire
Nationality	Nominal qualitative	Spanish Other	Ad hoc questionnaire
Educational level	Polytomous qualitative	Nursing Diploma Nursing Degree Master’s Doctorate	Ad hoc questionnaire
Sexual orientation	Polytomous qualitative	Heterosexual Homosexual Bisexual Asexual Other Prefer not to say	Ad hoc questionnaire
Primary care centre	Nominal qualitative	33 health centres in the MVGHD: Alameda–Perchel Alhaurín de la Torre Alhaurín el Grande Álora Alozaina Campanillas Capuchinos Carlinda Carranque Churriana Ciudad Jardín Coín Colonia Sta Inés-Teatinos Cruz de Humilladero Delicias El Cónsul El Palo Estación de Cártama Huelin La Luz La Roca Limonar Miraflores de los Ángeles Nueva Málaga Palma-Palmilla Portada Alta Puerta Blanca Puerto de la Torre Rincón de la Victoria San Andrés-Torcal Tiro Pichón Trinidad Jesús Cautivo Victoria	Ad hoc questionnaire
Type of employment	Nominal qualitative	Permanent Temporary Substitute	Ad hoc questionnaire
Years of experience in primary care	Ordinal qualitative	<1 year 1–5 5–10 >10 years	Ad hoc questionnaire
SABS Scale	Likert-type scale	Strongly disagree Disagree Neutral/Undecided Agree Strongly agree	SABS Instrument

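### Previous training in sexual diversity is a named predictor in the Phase I secondary outcome, but no list of survey variables collects it

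*Protocol article*

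**What the plan says.** Section 3.1.1 of the Protocol article sets the Phase I secondary outcome as the statistical relationship between sexuality-related attitudes and beliefs and a set of sociodemographic and professional variables, which it then names: "specifically age, sex, years of experience in primary care, and previous training in sexual diversity".

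The article says in three places what is collected:

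- **Section 4.2.3** gives the characteristics recorded by the ad hoc questionnaire as "age, sex, educational level, sexual orientation, primary care centre, employment type and years of experience in primary care", together with the 12 SABS items.
- **Section 4.2.4** describes the instrument as a whole: "The complete survey comprised: (1) an ad hoc section collecting sociodemographic data". The contents of that section are "age, primary care centre, nationality, sex, sexual orientation, educational level, employment type, and years of experience in primary care". The second and last part is "12 SABS items rated on a five-point Likert scale (1 = Strongly disagree to 5 = Strongly agree").
- **Table 1** lists the study variables with their response categories. Its educational-level row has the values "Nursing Diploma Nursing Degree Master’s Doctorate".

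On the role of the scale, section 4.2.4 states: "The SABS scale will be used to evaluate attitudes and beliefs around human sexuality in nursing".

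**The concern.** The outcome section promises an estimate that needs a value for each nurse's previous training. The instrument, as described, never asks for it. An analysis plan cannot repair this, because no choice of test recovers a variable that was not recorded. Phase I is a single cross-sectional survey and the article describes no re-contact of respondents, so an item left out at launch stays out.

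The variable matters to this project. The Rationale says the participants were chosen partly because their views reflect the effect of earlier training, and the Conclusions expect the results to point to a need for specialised training programmes. Whether trained and untrained nurses differ in their SABS responses is a natural Phase I question, and the secondary outcome asks it. Phase II is not designed to answer it instead: it plans 15 to 20 interviews, and the sampling characteristics named in section 4.3.2 are experience, educational level and health centre.

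**Working it through.** No formula applies. The check compares the four predictors in section 3.1.1 with each list of collected variables.

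| Predictor in 3.1.1 | 4.2.3 | 4.2.4 | Table 1 |
|---|---|---|---|
| Age | yes | yes | yes |
| Sex | yes | yes | yes |
| Years of experience in primary care | yes | yes | yes |
| Previous training in sexual diversity | no | no | no |

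Three of the four predictors are collected according to every list; one of the four is in none.

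**How complete are the lists?** Section 4.2.3 names seven ad hoc variables. Section 4.2.4 names eight, the addition being nationality. Table 1 has ten rows: the same eight, plus randomisation group and the SABS. So 4.2.3 is not a full itemisation, but 4.2.4 and Table 1 agree on the eight ad hoc variables, and 4.2.4 presents its list as the complete survey.

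**Could a listed variable stand in?**

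- *Educational level.* Its four categories are academic awards. They do not say whether the holder was taught about sexual diversity, and they do not capture continuing education. The Rationale reports that one university's nursing degree has included a compulsory Gender and Sexual Health subject since 2011. Neither the university attended nor the year of qualification is collected, so the award does not identify who took that subject.
- *Age and years in primary care.* These are separate predictors in the same outcome, recorded in bands. Neither identifies exposure to a particular course.
- *The SABS items.* Their wording is not reproduced in the article. They are described as agreement ratings used to evaluate attitudes and beliefs, and nothing in the article presents them as a record of training. They are also the dependent measure in this analysis.

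**Is training measured elsewhere?** Other mentions of training, in the Introduction, Rationale, Discussion and Conclusions, are background, motivation or expected implication. None describes a measured variable.

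**The case against.** The strongest reply is that this may be an omission from the article and not from the questionnaire. The questionnaire is not shown and the lists are loosely drafted: 4.2.3 leaves out nationality, and Table 1 gives the ad hoc questionnaire as the source of the randomisation group, although section 4.2.4 has an independent researcher generate the allocation. That is fair as a limit on certainty. A reader might infer that none of the 112 respondents will have a training value; the documents support only the narrower statement that the survey, as described, does not collect one. The reply does not remove the point. The list in 4.2.4 is offered as complete, Table 1 matches it, and both have room for nationality but not for a predictor that the outcome names. This is a stated outcome at odds with a stated instrument, not ordinary condensation.

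A second reply is that the case for training does not hang on this variable. That stands. A reader might infer that training history is the only Phase I evidence on training need, or that the expected conclusion is left without support. The documents do not bear that out: the SABS scores and the contrast between the two questionnaire versions also bear on it, as does the Phase II discourse work. An observational association with past training would be one further strand, itself open to confounding.

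Third, educational level may carry some information, since Table 1 separates the diploma from the degree. The article also does not establish how far training varies within one award. It remains true that the award does not measure the named variable.

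Finally, the effect is confined to one predictor of a secondary outcome in a study described as a pilot. That is correct and sets the severity.

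**Conclusion.** The point holds in limited form. One of the four predictors named in the Phase I secondary outcome is absent from all three variable lists, and no listed variable can take its place. If the survey is fielded as described, that part of the secondary outcome cannot be estimated. The primary outcome, the comparison of the two questionnaire versions and the other three predictors are untouched. One in four is a count of named predictors; it does not measure bias or lost information.

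The conclusion assumes that the survey matches its description in section 4.2.4. If the actual questionnaire already has a training item, the defect is one of reporting, and correcting the three lists would settle it. Severity: should be fixed, before launch.

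**What to change.** Add one item with defined response categories on previous training in sexual diversity or LGBTQ+ health. Place it after the 12 SABS items: the Group B introduction deliberately leaves out sexual orientation and gender identity, and an earlier question on sexual-diversity training would prime those respondents. List the item, with its categories, in sections 4.2.3 and 4.2.4 and in Table 1.

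No new method is needed. Section 4.2.5 already provides the Mann–Whitney U test with rank-biserial correlation for two groups, and the Kruskal–Wallis test with epsilon-squared for more than two. Year of qualification would be a useful optional extra but is not required.

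If the item cannot be added, remove previous training from the secondary outcome in 3.1.1 so that the outcome and the instrument agree.

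The cost is one extra survey item and any ethics notification it requires; the article does not say what that would be. The timing relies on the Data Availability statement, which says no data have yet been generated. Two other places read as though Phase I were further along: section 4.2.4 describes the survey in the past tense, and section 4.3.1 refers to a bias already detected in Phase I. The authors should confirm that the survey has not been launched. If it has, only the removal remains, unless the item was in fact asked.
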